## Abstract

**Highlights:**

**What are the main findings?**
This is the first study applying AOT specifically to promote upper-limb skills in children and adolescents with diplegic CP. The study adopts a home-based AOT protocol, supported by remote clinical supervision, which increases accessibility for families and allows for a more intensive and flexible delivery of the intervention.The AOT home intervention could be tailored to the different features of children with diplegic CP, allowing video selection from a large, diversified library of actions, making it adaptable to individual needs.

**What is the implication of the main finding?**This study will contribute in building evidence on the efficacy of AOT for diplegic CP, with possible positive effects on daily-life functional tasks and indirect benefits on postural control and balance. Moreover, demonstrating its feasibility could support the wider adoption of AOT in other neurodevelopmental or motor conditions.Through a combination of motor and neuropsychological assessments, the project aims to provide insights into the cognitive components of manual action, such as action planning.
The integration of neuroimaging will allow investigation of AOT-induced neuroplasticity and its association with clinical changes.

**Abstract:**

**Background**: Children with diplegic Cerebral Palsy often exhibit upper-limb (UL) motor impairments compounded by deficits in visuospatial, sensory, and executive functions. Despite this, research has primarily focused on lower-limb rehabilitation, leaving the treatment of UL function in diplegic Cerebral Palsy underexplored. Action Observation Therapy (AOT), based on Mirror Neuron System activation, has shown promise in promoting motor recovery, but evidence specific to this population is limited. This exploratory randomized controlled trial (RCT) aims to assess the feasibility and effectiveness of a home-based AOT program—ACT ON DIP—for improving upper-limb function in children and adolescents with diplegic Cerebral Palsy. **Methods**: Fifty-four participants with spastic diplegic Cerebral Palsy (MACS and GMFCS levels I–III, aged 5–16 years) will be randomly assigned to an experimental group (receiving an 8-week home-based AOT program) or a control group (receiving standard care). The ACT ON DIP system includes an ad hoc software, kits of objects for daily tasks, and wearable sensors. The system allows for delivering structured uni- and bimanual AOT activities tailored to the child’s profile. Primary outcome is the Both Hands Assessment (BoHA); secondary outcomes include motor (MA-2, BBT, ABILHAND), neuropsychological (NEPSY-II, Corsi Test, BRIEF), and participation measures (COPM, PEM-CY, CP-QOL). A subgroup will undergo fMRI to explore neural correlates of training-related changes. **Results**: Feasibility, compliance, and user experience with the home-based system will be assessed. This study will evaluate short-, medium-, and long-term changes in UL performance and related neuropsychological functions. **Conclusions**: ACT ON DIP represents a novel, personalized, and accessible tele-rehabilitation intervention for children with diplegic Cerebral Palsy. If effective, it could expand treatment opportunities for UL rehabilitation in this population and support broader implementation of home-based AOT.

## 1. Introduction

Cerebral Palsy (CP) is the most represented cause of physical disability with childhood onset, with an incidence between 1.6 and 3.3 out of 1000 [1]. It is defined as a heterogeneous group of disorders affecting the development of movement and posture [2]. The causes are most often represented by non-progressive brain injury or lesion acquired during the prenatal, perinatal, or early postnatal period. CP exhibits a wide range of clinical presentations depending on several factors, including the nature, extent, severity, and timing of the brain injury [3]. For this reason, classifying the different forms is a challenge, and many different classification systems are used [4]. The Surveillance of Cerebral Palsy in Europe classification identifies three types of CP: ataxic, dyskinetic, and spastic. The spastic form accounts for about 90% of cases and presents itself in both unilateral and bilateral forms [5]. Within the bilateral forms, many authors agree on the need to differentiate between severe and equivalent involvement of the four limbs, and an unbalanced affection of mainly lower and in part upper limbs. This allows for the differentiation between spastic tetraplegic and diplegic CP (first and second case, respectively), such as in Ingram’s and Hagberg’s classification systems [5,6]. The diplegic form of CP, the most frequent in preterm babies, accounts for approximately 44% of all CP cases. The main aspect that defines spastic tetraplegic and diplegic CP is the use of the upper limbs (ULs), which, together with better cognitive and sensory abilities and lower severity of associated factors, grants children with diplegic CP a higher degree of autonomy than those with tetraplegic CP [7]. In fact, in children with diplegic CP, a wider UL motor repertoire is primarily linked to the ability to use walking aids or to achieve independent walking and effective autonomy [8]. Probably linked to this, many recent works [8,9] are mainly focused on UL movement patterns during walking. The research on UL use in children with diplegic CP seems to remain relatively scarce, although it is an important aspect.

Indeed, approximately 60–70% of children with bilateral spastic CP show reduced ULs functionality [10,11]. Children with diplegic CP show impaired manual skills often caused by specific motor limitations, such as the presence of spasticity and coordination issues.

In this direction, a systematic review [12] collected fifteen studies, which presented a wide variety in the intervention content and in the outcome measures, impeding a meaningful synthesis of results. Among the analysed studies, a good quality is reached by the HABIT or HABIT-ILE treatment [13,14], which showed to have a role in promoting the UL skills, but with particular respect to the dominant hand. These authors reported that this could be due to the role of the two hands in gross motor activities and the need of the ULs, and particularly the non-dominant one, to support the stabilization of the posture. In addition, the selected primary outcome measure Both Hands Assessment (BoHA) may not be sufficiently sensitive to detect changes in the magnitude resulting from the HABIT intervention in relation to participants’ characteristics. There is also an example of a technological intervention specifically focused on UL skills in children with diplegic CP that is proposed (Armeo^®^ Spring): in a pilot study [15], it resulted in an improvement at clinical scales, often transferred also in everyday life activities in areas not directly trained, such as self-care, suggesting that the technological context highly enhances the motivation.

Anyway, the aforementioned review [12] suggests that further studies are needed, by respecting a high-quality methodology, by isolating the intervention under exam and avoiding interventions that comprise more than one component, and by selecting the specific population on the basis of specific classification systems. Finally, they sensibilize on the use of appropriate outcome measures.

In addition to this, to our knowledge, an aspect that seems to be lacking is the inclusion and investigation of extra motor factors, since the motor impairments are shown to be mostly caused and/or accompanied by extra motor factors [16], such as the visual-perceptual impairment [17] and the altered sense of agency [18]. More specifically, diplegic CP causes impairments in the acquisition, integration, and interpretation of multisensory information originating from both somatic and environmental sources. Such impairments are particularly evident in processing spatial and temporal characteristics of sensory input, which constitute critical substrates for the planning, modulation, and execution of purposeful and coordinated motor behaviour [19,20,21,22].

Beyond motor impairments, CP also affects cognitive functioning, which is shown to be linked to manual functions. The planning function is known to be particularly affected [22]. Specifically, children with diplegic CP often show a discrepancy between Verbal IQ (VIQ) and Performance IQ (PIQ), with a relative advantage in VIQ [23]. Additionally, difficulties in visuospatial and sensorimotor abilities, executive functions, selective attention, and inhibitory control have been documented [24]. Several studies have highlighted associations between motor impairments, attention deficits, and impulsive response styles, which may hinder the acquisition of bimanual motor skills [25,26].

As described above, UL function in children with diplegic CP is characterized by varying degrees of motor impairment, further complicated by deficits in perceptual and cognitive abilities. These factors result in a highly complex clinical picture; thus, caring for these abilities requires specific attention and should be taken into account when defining the goals and contents of rehabilitation.

In the framework of UL rehabilitation, one of the most recently used approaches is Action Observation Therapy (AOT), based on the Mirror Neuron System (MNS) properties. Specific regions within the Mirror Neuron System (MNS), including the ventral premotor cortex and the inferior parietal cortex, are active during both the execution and observation of goal-directed motor actions [27].

Although most of the evidence about the effectiveness of AOT involves adults [28,29], recent meta-analysis [30] focusing on studies involving stroke patients or subjects with CP reported improvements in upper- and lower-limb motor function in adults, as well as UL motor function in children. In detail, promising insights into AOT effectiveness came from studies on children with unilateral CP, demonstrating improvements in UL performance, daily activities, and motor skills after an AOT training carried out at the clinic [31]—additionally, with higher improvements, at home [32,33],.

However, a recent review [34] found that the effectiveness of AOT training on children with Cerebral Palsy may be overstated; this seems to be linked to a wide heterogeneity in the characteristics of the recruited population, as all the clinical forms of CP were included in the majority of studies. This prompted the need to investigate the effects of AOT by selecting a more restricted category of subjects with CP.

In addition, few studies have explored the effects of rehabilitation on the structure and function of the central nervous system in children with CP, such as a recent study [35], which observed brain modifications correlated with functional improvements in children with unilateral CP. Another study reported that, in children with unilateral CP, AOT treatment based on the observation and imitation of pathological models—that is, other children with CP—leads to increased activation of the Mirror Neuron System, as well as enhanced activation of subcortical areas such as the sensorimotor thalamus [36].

New Information and Communication Technologies (ICTs) represent one of the most promising means of offering personalized rehabilitation interventions directly in the patient’s home environment; they also allow continuous monitoring of treatment by clinical staff and enhance the motivation of the participants [37]. As highlighted by recent studies [32,38], it is therefore possible to use new technologies to deliver AOT treatments directly to patients’ homes. In fact, the use of technological platforms allows a large number of patients to have access to innovative, intensive, and personalized treatments in their home environment. Further investigation, particularly randomized controlled trials (RCTs), is needed to better understand the mechanisms of brain plasticity in children with neurological injuries. In fact, larger and more rigorous studies could help strengthen the scientific evidence supporting innovative training such as AOT, enabling the standardization of its use and the identification of individual factors, in order to develop personalized approaches.

Within this framework, the ACT ON DIP project (ACTion Observation tele-rehabilitatioN for upper limb in children with DIPlegic Cerebral Palsy), designed as an exploratory RCT, aims to first assess the feasibility and then to investigate the effectiveness of UL AOT training on children and adolescents with diplegic CP. Specifically, the AOT will be provided at home by means of a dedicated technological system.

## 2. Materials and Methods

### 2.1. Study Design

The project is a non-profit two-arm exploratory randomized clinical study consisting of an experimental group and a control group. Recruitment, clinical experimentation, and analysis of all clinical, technological, and neuroimaging data will be carried out by the centres involved in the study: IRCCS Fondazione Stella Maris (Pisa), AUSL IRCCS of Reggio Emilia, University of Parma. The recruitment will be carried out by some staff members (who will not have access to the allocation sequence), which will be responsible for the identification of eligible children; then, a different group of staff members will take care of randomly assigning the enrolled children to the study groups.

After fulfilling the inclusion and exclusion criteria described below and obtaining signed informed consent, enrolled participants will undergo an initial baseline assessment (T0) and will be block-randomized (ratio 1:1) in the experimental group (EG) or the control group (CG), using a computer-generated set of random numbers by an independent operator. The EG will carry out an 8-week AOT period, while the CG will continue standard care; that is, they will continue their usual care without receiving any additional training (details in Section 2.5).

Families from both groups will be asked to complete a diary to track daily activities and therapies throughout all 8 weeks. After this period, both groups will be assessed again (T1). T1 will be the primary endpoint aimed at evaluating the short-term effects of AOT. All participants will also be evaluated at 8 and 24 weeks (T2 and T3, respectively) after T1 (Figure 1) to evaluate the medium- and long-term effects of AOT. Details of the AOT training and the adopted outcome measures are described below.

The clinical team asked the FTS foundation—an association composed of families of children with CP—for support in participant enrolment and involvement. They are actively participating in this study, particularly in awareness campaigns and participant enrolment. After the study’s completion, the FTS foundation will help the consortium involve families in reporting their experiences and be informed about the study results in a joined final event.

### 2.2. Participants

Participant recruitment will be conducted by the two clinical centres involved in the project, in accordance with predefined inclusion and exclusion criteria (IRCCS Fondazione Stella Maris and AUSL IRCCS of Reggio Emilia), selected within databases that collect data of subjects who have previously given consent to receive information and proposals for new research protocols, and among patients referring to the above-mentioned structures for functional assessments and/or rehabilitation care. Eligible subjects and their families will subsequently receive invitations to participate in the study, and informed consent will be obtained from the subjects and/or their caregivers before enrolment. Subjects will be recruited based on the following specific inclusion criteria:Confirmed diagnosis of spastic diplegic Cerebral Palsy;Age between 5 and 16 years at the time of recruitment;Manual Ability Classification System (MACS) levels I–III [39];Gross Motor Functional Classification System (GMFCS) levels I–III [40];At least one cognitive functioning index greater than −2 standard deviations, assessed with a battery of standardized tests such as WISC-IV or WISC-V, in order to ensure a sufficient level of comprehension and cooperation in the proposed activities.

Moreover, the following exclusion criteria will be applied:Presence of uncontrolled epilepsy;Injection of botulinum toxin or orthopaedic surgery in the upper limb carried out in the previous 6 months or planned during the study period.

Participants will be removed from the study regardless of their allocation group if any of the following conditions are met:They begin an intensive treatment program;They require a botulinum toxin injection before the end of the study;Other adverse events occur that prevent further participation.

A subgroup of patients from EG and CG will be selected to perform a functional magnetic resonance imaging (fMRI) assessment. For these participants, additional exclusion criteria will be the following:Insufficient cooperation during approximately 30 min long neuroimaging studies;Presence of exclusions for 3T MRI investigations (as metal implants, prostheses, shunts, etc.). These exclusions will be checked using an ad hoc questionnaire.

Moreover, a subgroup of age-matched typically developing (TD) children, recruited on a voluntary basis, will be also enrolled as healthy control group.

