### 2.3. Sample Size

For the present study, a minimum size of 21 subjects per group is required to obtain a difference of at least 5 BoHA units at a significance level of 0.05 and a power of 80%. Considering a possible dropout of 20%, at least 27 subjects per group will be recruited, for a total sampling of at least 54 children with diplegic Cerebral Palsy. The minimum sample size was computed using the G*Power software v 3.1 9.6.

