A subgroup of children will carry out also other technological assessments with the Virtual Reality Rehabilitation System (VRRS). The measurement of manual skills will be carried out through a set of evaluative VRRS tasks, aimed at quantitatively and objectively estimating and measuring manual abilities using kinematic movement parameters. Furthermore, the Upper Limb TRAcker (ULTRA+) biomechatronic system will be used to measure manual skills. This system provides measurements of both kinematic parameters and grip force.

Technological analysis, along with test and questionnaire scoring, will be conducted after the completion of all timepoint assessments. To maintain study blindness, the tests and questionnaires will be scored by personnel not directly involved in the training or SC supervision, i.e., personnel blind to the allocation group and the timepoint. When this is not be possible, all required data will be anonymized and randomized in order to hide the assessment timepoint.

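### All MACS I–III children are eligible, but the randomisation and T1 comparison as described take no account of MACS, leaving avoidable variance in the BoHA result

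*Protocol article*

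**What the plan says.** - **Entry (Section 2.2):** "Manual Ability Classification System (MACS) levels I–III [39". The other inclusion criteria are diagnosis, age, GMFCS level and a cognitive index. None asks for reduced upper-limb function.
- **Background (Section 1):** "approximately 60–70% of children with bilateral spastic CP show reduced ULs functionality". The same section says, of earlier trials with BoHA as primary outcome, that it "may not be sufficiently sensitive to detect changes in the magnitude resulting from the HABIT intervention", and ties this to participants' characteristics without saying which.
- **Randomisation (Section 2.1):** participants "will be block-randomized (ratio 1:1) in the experimental group (EG) or the control group (CG") from computer-generated random numbers. No stratification factor is named.
- **Sample size (Section 2.3):** taking alpha as 0.05 and power as 80%, the article states that "a minimum size of 21 subjects per group is required to obtain a difference of at least 5 BoHA units at a significance level of" that size. On attrition it adds: "Considering a possible dropout of 20%, at least 27 subjects per group will be recruited". The total is 54. No SD is given.
- **Timing of scoring (Section 2.6):** technological analysis, "along with test and questionnaire scoring, will be conducted after the completion of all timepoint assessments".
- **Analysis (Section 2.8):** the groups are compared at T0 and then at T1, with follow-up compared with baseline as a second level. No covariate is named for the T1 comparison.

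**The concern.** The trial asks whether training improves upper-limb function, yet it can enrol children at the mild end of manual ability. Two things follow.

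First, manual ability is likely to be related to the BoHA score. If nothing in the allocation or the analysis accounts for it, chance differences in MACS mix between two small arms become noise in the T1 difference.

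Second, if some children have little to gain on BoHA, the mean difference falls below the effect in the remaining children. Section 2.3 makes no visible allowance for this in its 5-unit target.

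The first is fully under the sponsor's control. MACS is an entry criterion, so it is known before allocation. T0 BoHA cannot serve for stratification, because scoring waits until all assessments are complete, but it can still be a covariate.

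**Working it through.** **1. The plan's own figures.** 21 / (1 − 0.20) = 26.25, rounded up to 27 per group and 54 in total, as stated. The 21 cannot be reproduced directly because no SD is given. Solving the two-sample t-test (noncentral t, two-sided 0.05, 80% power, n = 21 per group) for the standardised difference gives d = 0.886, so SD = 5 / 0.886 = 5.64. If the test were one-sided, d = 0.781 and SD = 6.40. The article states neither SD nor the sidedness. The two-sided value is used below.

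**2. Chance imbalance in MACS.** Assume a share p of 30–40% at MACS I; the article gives no expected mix. The SD of the between-arm difference in share is √(2p(1−p)/27):
- p = 0.30: √(0.42/27) = 0.125
- p = 0.40: √(0.48/27) = 0.133

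That is about 12–13 percentage points. An exact hypergeometric calculation for 16 or 22 MACS I children among 54 gives 12.5 and 13.5 points. The chance that the arms differ by at least 20 points is 13.5% and 16.6% respectively.

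**3. What this means for BoHA.** Assume a 5-unit gap D between MACS I and II–III, and read 5.64 as the total SD of the T1 score. Variance due to MACS is p(1−p)D²:
- p = 0.30: 0.21 × 25 = 5.25; 5.25 / 31.8 = 16.5%
- p = 0.40: 0.24 × 25 = 6.00; 6.00 / 31.8 = 18.9%

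So MACS carries about 17–19% of the outcome variance. The standard error of the T1 difference at 27 per arm is 5.64 × √(2/27) = 1.54. The part due to MACS imbalance has SD 5 × 0.125 = 0.62 to 5 × 0.133 = 0.67 units. Removing it would bring the standard error to 1.54 × √(1 − 0.165) = 1.41 or 1.54 × √(1 − 0.189) = 1.39, a reduction of about 9–10%.

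**4. How large the gap can be.** An SD of 5.64 bounds D, since p(1−p)D² cannot exceed 31.8. D is at most 5.64/√0.21 = 12.3 units at p = 0.30 and 5.64/√0.24 = 11.5 units at p = 0.40, even with no variation within MACS groups.

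**5. Dilution, as a sensitivity range only.** Let a share f gain nothing and the rest gain 5 units, so that the mean difference is 5(1 − f). With 21 per group and SD 5.64:

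| f | Mean difference | Power |
|---|---|---|
| 10% | 4.5 | 71% |
| 20% | 4.0 | 61% |
| 30% | 3.5 | 50% |
| 40% | 3.0 | 39% |

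Allowing for the extra variance of a mixed response lowers the last two to 47% and 36%. Under a one-sided test (SD 6.40, without that extra variance) they would be 54% and 44%.

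**The case against.** The strongest reply is that chance imbalance is not bias. A randomised comparison's standard error already includes it, and an unadjusted test remains valid. That stands: the gain from stratifying and adjusting is precision and face validity, not rescue of an invalid test.

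A reader might infer that 30–40% of the enrolled children have no deficit and cannot improve, so that power is really 39–50% and a null result could not be interpreted. The documents do not support this. The 30–40% is only the complement of a figure for all bilateral spastic CP. The Introduction goes on to describe children with diplegic CP as having impaired manual skills, and nothing equates MACS I with absence of deficit. No BoHA ceiling is reported, and the remark on BoHA sensitivity does not single out mild children. Exercises are chosen partly by manual ability and become harder over time (Section 2.4). The trial is exploratory, measures several other upper-limb outcomes, and plans an analysis of baseline predictors of response (Section 2.8).

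A reader might also suppose that a MACS gap of up to 20 BoHA units could swing the T1 result by itself. Step 4 rules this out under the SD implied by the sample size.

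Finally, the article is condensed, and a fuller protocol may name strata or covariates. If so, that part of the recommendation is already met. If the implied SD is one of change rather than of T1 score, level differences between MACS groups largely cancel and the precision gain shrinks. The article does not say which it is.

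**Conclusion.** The point holds as one of avoidable variance. Entry spans MACS I–III with no required deficit, and neither the described randomisation nor the T1 comparison uses MACS. The expected imbalance is moderate: an SD of about 12–13 percentage points in the MACS I share, if that share is 30–40%. MACS would carry about 17–19% of the BoHA variance, given a 5-unit gap and a T1-score SD of about 5.6. The share, the gap and the reading of the SD are assumptions. No systematic bias follows.

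Dilution is a legitimate question for the sample size, but its size is unknown. The 71% to 39% power range shows sensitivity to the unknown share and is not an estimate for this trial.

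**What to change.** 1. Stratify the block randomisation by MACS level (I versus II–III). The level is known at screening. Cost: separate randomisation lists.
2. Name MACS level and T0 BoHA as covariates in the T1 BoHA comparison. T0 BoHA may take up much of what MACS explains, but the stratification factor belongs in the model. T0 BoHA is assessed in any case and its late scoring is no obstacle. Cost: one extra model term for MACS.
3. State the SD and the expected MACS mix behind the 5-unit target, and show the dilution range beside it as a sensitivity analysis. Cost: a few sentences.

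An added deficit requirement for MACS I children, such as a threshold on ABILHAND-Kids, is not recommended. The documents support no threshold, the rule would narrow the range of manual ability that this exploratory trial has chosen, and relying on a T0 questionnaire would exclude children after enrolment and assessment.

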### 2.5. Standard Care

Participants originally allocated to the CG will pursue their usual care for 8 weeks.

Standard care for children with CP in Italy is provided primarily through the Italian National Health Service, which ensures access to care through a network of public and accredited rehabilitation facilities. The model of care is coordinated and multidisciplinary, typically involving professionals in child neuropsychiatry, physiotherapy, childhood neuromotor development therapy, speech and language therapy, psychology, orthopaedics, and social services. Despite the broad availability of services, access and quality of care may vary across regions due to differences in resource allocation, staffing, and waiting times. Moreover, the dose and the content of the standard care are often negligible in having a meaningful impact on the short-term outcome, particularly among adolescents. Due to ethical reasons, it is not possible to ask to interrupt the traditional standard care, and in this sense, the participation in the ACT ON DIP project does not intend to interfere with the traditional care, so no other standard intervention will be forbidden to participants of both groups.

During this period, participants will be asked to wear Actigraphs on both wrists.

Families of children in both groups will be asked to complete a daily diary during the 8-week training period, providing details regarding the frequency, duration, and type of all the main therapies, routines, and activities performed. The diary will have a daily checklist of the most common daily life activities, wake-up and school times. The daily diary will also include a guide on correctly using and managing the given wearable sensors.

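### Removing randomised children from the study when they start an intensive programme or need botulinum toxin leaves later outcomes uncollected and can bias the group comparison, by an amount the protocol does not allow one to determine

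*Protocol article*

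**What the plan says.** Section 2.1 sets the order of events: "enrolled participants will undergo an initial baseline assessment (T0) and will be block-randomized (ratio 1:1"). Both groups are assessed at T1, after the 8-week period, which is the primary endpoint. T2 and T3 follow 8 and 24 weeks after T1 and are described as covering all participants.

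Section 2.2 then gives a removal rule: "Participants will be removed from the study regardless of their allocation group if any of the following conditions are met". The three conditions are:
- "They begin an intensive treatment program"
- "They require a botulinum toxin injection before the end of the study"
- "Other adverse events occur that prevent further participation"

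The consequence is removal from the study. The article does not describe stopping the training while assessments continue.

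Two other statements bear on the rule. The entry exclusion in Section 2.2 reads "Injection of botulinum toxin or orthopaedic surgery in the upper limb carried out in the previous 6 months or planned during the study period", so it mentions the upper limb, while the removal condition names no limb. Section 2.5 explains that usual care is not interrupted, "so no other standard intervention will be forbidden to participants of both groups".

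Section 2.3 requires 21 children per group for a 5-unit BoHA difference at 80% power. It raises this to 27 per group for 20% dropout.

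**The concern.** The conditions are met after allocation, so the children who remain are selected by post-randomisation events. Applying the same rule in both arms gives no assurance that it removes the same number, or the same kind, of children from each.

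The design gives reasons why it might not. Allocation cannot be hidden from families, because the training system is installed at home. Controls continue usual care with nothing added, and Section 2.5 itself describes that care as often too slight to matter in the short term, so control families may look for an intensive programme. The need for an injection, or the wish for more therapy, may reflect how the child is progressing. Blinded scoring (Section 2.6) protects the measurement but has no influence on who is left to be measured.

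If removal differs by arm and is related to outcome, the comparison of remaining children is biased. An analysis-set definition in a separate SAP could not repair this, because it cannot restore assessments that were never made. The 20% dropout allowance protects numbers and does nothing for comparability.

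**Working it through.** **Exposure window.** T1 is 8 weeks after the start, T2 is 8 + 8 = 16 weeks, and T3 is 8 + 24 = 32 weeks. Only events in the first 8 of 32 weeks (25%) can remove a child before the primary endpoint.

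**The plan's own figure.** 21 / (1 − 0.20) = 26.25, rounded up to 27 per group and 54 in total. This reproduces Section 2.3. No SD is given. Back-solving a two-sided two-sample t-test with 21 per group and 80% power gives d = 0.886, an implied SD of 5 / 0.886 ≈ 5.64 BoHA units. One-sided, d = 0.781 and the SD is about 6.40. I use 5.64 below as an assumption.

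**Simple formula.** If a share r of an arm is removed, the mean of those retained differs from the full-arm mean by r × (gap between retained and removed). With no removal in the other arm, that is also the bias in the group difference. The document gives neither r nor the gap, so both are assumed:
- r = 10%, gap 5: 0.10 × 5 = 0.5 units
- r = 20%, gap 5: 0.20 × 5 = 1.0 unit (20% of the 5-unit target)
- r = 20%, gap 10: 0.20 × 10 = 2.0 units

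A 5-unit gap is 5 / 5.64 ≈ 0.9 SD and a 10-unit gap about 1.8 SD, so these are large contrasts.

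**Separating T1 from later visits.** Suppose 20% of one arm were removed by T3, evenly over time, with a 5-unit gap. By T1 the share is 20% × 8/32 = 5%, a bias of 0.25 units. By T2 it is 20% × 16/32 = 10%, or 0.5 units. By T3 it is 1.0 unit.

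**Simulation.** 27 per arm, SD 5.64, no true effect, removal tending to take lower-scoring children, two-sided t-test on those remaining, 20,000 runs. Bias is experimental minus control, in BoHA units.

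| Removed EG / CG | Removal–outcome correlation | Bias | Type I error |
|---|---|---|---|
| 20% / 20% | 0 to 0.7 | about 0 | 4.8–6.7% |
| 10% / 30% | 0 | about 0 | 4.8% |
| 10% / 30% | 0.3 | −0.45 | 5.9% |
| 10% / 30% | 0.5 | −0.81 | 8.2% |
| 10% / 30% | 0.7 | −1.09 | 11.8% |
| 5% / 35% | 0.7 | −1.78 | 20.1% |
| 30% / 10% | 0.3 | +0.46 | 6.2% |
| 30% / 10% | 0.7 | +1.07 | 11.5% |

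The sign follows whichever arm loses more children. Every unequal row averages 20% removal, so this rule alone would use up the whole dropout allowance. These are severe scenarios.

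**Wording of the botulinum toxin criteria.** If the upper-limb qualifier in the entry exclusion covers the injection as well as the surgery, a child with an injection planned elsewhere is eligible, can be randomised, and must then be removed. Section 1 describes diplegia as affecting mainly the lower limbs, so the case is not remote. If the qualifier covers surgery only, the two statements agree. The text permits both readings.

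**The case against.** The strongest reply is that the harm is only possible. The article gives no removal rates, and bias is about nil if removal is balanced or unrelated to outcome. Exposure before T1 is short, and at least some planned injections and surgery are already excluded at entry. Section 1 cites a call to isolate the intervention under study, and withdrawing children who start a competing programme serves that aim. After an adverse event that prevents participation, further assessment may be impossible. All of this stands. It limits the claim to a risk and confines the main remedy to the first two triggers.

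Four stronger readings may tempt a reader, and the document does not support them:
- **That the randomised comparison is broken.** The text shows only that it can be biased. That families doing daily sessions have less time for another programme is plausible but stated nowhere.
- **That there is almost no sample-size slack, because 27 × 0.8 = 21.6 against 21.** The step from 21 to 27 is the slack. Nothing says that removals come on top of "Considering a possible dropout of 20"%.
- **That a completed T1 value is discarded when a child is removed later.** The article does not say so, and handling of data collected before withdrawal may be set out elsewhere.
- **That Section 2.5 flatly contradicts Section 2.2.** Section 2.5 concerns standard interventions and the trigger concerns an intensive programme. Withdrawal is also not prohibition. How the two fit needs clarifying, but this is no firm conflict.

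The objection does not answer the central point. The rule as written ends participation for randomised children, and outcomes not collected cannot be recovered at analysis.

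**Conclusion.** The concern holds as a design weakness with a possible, unquantified bias. It is smaller in prospect at T1 (events in the first 8 weeks) and larger at T2 and T3 (events over 16 and 32 weeks). The illustrative figures of roughly 0.5 to 2.0 BoHA units depend wholly on assumed removal rates, an assumed gap or correlation and, in the simulation, an SD back-solved from the sample size. The upper end needs extreme inputs, and none of the figures is an estimate for this trial. Direction is equally open.

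The trial is described as exploratory and puts feasibility first, so this does not undermine the whole plan. It should still be changed, because the remedy is cheap beforehand and unavailable once visits have been missed. The botulinum toxin wording in Section 2.2 is a separate ambiguity and needs reconciling on its own account.

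**What to change.** 1. For the intensive-programme and botulinum toxin triggers, replace removal from the study with continued T1, T2 and T3 assessment wherever the family agrees. For adverse events that prevent participation, continue assessment only where possible.
2. State that all outcomes already collected are kept, including a T1 BoHA obtained before the event.
3. Make the primary analysis a comparison of all assessed children in their randomised group, whatever co-treatment they received (a treatment-policy strategy).
4. Record these events as intercurrent events, with dates, and report them by arm. The family diary covers only the 8-week period, so ask about them at T2 and T3 as well.
5. Add a sensitivity analysis that leaves out post-event data.
6. Reconcile the entry exclusion and the removal rule on botulinum toxin, and say how the removal rule fits with Section 2.5. This review takes no view on which clinical rule is right.

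The cost is protocol wording, one added question at two visits, and assessments that are already scheduled. The statistical downside is that co-treatment may dilute the contrast, which the sensitivity analysis would show. The gain includes numbers: under the assumed SD of 5.64, power for 5 units is about 89% with 27 per arm and 80% with 21, so each child kept in follow-up helps.
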